## Abstract

**Background:**

Evidence suggests that dental anxiety and phobia are frequently the result of direct associative fear conditioning but that pre-exposure to dental stimuli prior to conditioning results in latent inhibition of fear learning. The mechanisms underlying the pre-exposure effect in humans, however, are poorly understood. Moreover, pain sensitivity has been linked to dental fear conditioning in correlational investigations and theory suggests it may moderate the latent inhibition effect, but this hypothesis has not been directly tested. These gaps in our understanding are a barrier to the development of evidence-based dental phobia prevention efforts.

**Methods:**

Healthy volunteers between the ages of 6 and 35 years will be enrolled across two sites. Participants will complete a conditioning task in a novel virtual reality environment, allowing for control over pre-exposure and the examination of behaviour. A dental startle (a brief, pressurized puff of air to a tooth) will serve as the unconditioned stimulus. Using a within-subjects experimental design, participants will experience a pre-exposed to-be conditioned stimulus, a non-pre-exposed to-be conditioned stimulus, and a neutral control stimulus. Two hypothesized mechanisms, changes in prediction errors and attention, are expected to mediate the association between stimulus condition and fear acquisition, recall, and retention. To ascertain the involvement of pain sensitivity, this construct will be measured through self-report and the cold pressor task.

**Discussion:**

Dental phobia negatively affects the dental health and overall health of individuals. This study aims to determine the mechanisms through which pre-exposure retards conditioned dental fear acquisition, recall, and retention. A randomized control trial will be used to identify these mechanisms so that they can be precisely targeted and maximally engaged in preventative efforts.

## Introduction

In the United States, dental fear and anxiety are prevalent issues that impact the oral health of 40–50 million Americans [1]. Moreover, Hispanic and African American populations are disproportionally impacted by poor oral health [2, 3], with dental fear as a common reason for avoiding dental visits in these populations [4]. A major etiological factor for dental fear is direct associative conditioning [5] but natural history studies suggest that pre-exposure to dental stimuli prior to a fear conditioning event can result in latent inhibition (LI), the retardation of associative conditioning as the result of prior learning [6, 7]. These findings suggest pre-exposure to dental stimuli as a method by which the development of dental fear and phobia could be prevented. However, the causal effect of LI on dental fear has not been established using experimental methods.

Moreover, to effectively harness the potential of LI to prevent dental fear, the underlying mechanism(s) must be better understood. Hall and Rodriguez ([8], see Fig. 1) have proposed a model of LI which starts with the well-established finding that a novel stimulus garners significant attention because of its potential to serve as a signal of a relevant event [9]. The model suggests that if the stimulus is not followed by a relevant event upon early presentations, a stimulus → no event association is learned. Over time, prediction errors (i.e., stimulus → event) are expected to decrease because of this learning, in turn, resulting in a decrease in attention as the lack of relevance of the stimulus is learned. If a pre-exposed stimulus is later paired with a relevant outcome (i.e., an unconditioned stimulus, UCS), this lack of attention renders the stimulus less available to enter an association with the UCS, retarding learning. Thus, changes in prediction errors (i.e., a decrease in the prediction that a stimulus will be followed by an event) and the ensuing decreased attention to the pre-exposed stimulus may be the mechanisms through which pre-exposure results in the LI effect.

**Fig. 1 Fig1:**
[figure not shown]
Hall and Rodriguez model

The Hall and Rodriguez model [10] also suggests that individual differences and manipulations that increase attention during pre-exposure should result in better learning of the stimulus → no event association and, in turn, larger LI effects. Indeed, this prediction has been borne out in animal studies (e.g., [11]). In humans, pain sensitivity is one characteristic that might function to increase attention to possible predictors of pain and therefore, greater LI with pre-exposure. However, this hypothesis has not yet been tested experimentally in humans.

Using an experimental design, the current study will determine if pre-exposure retards conditioning to a noxious oral stimulus and impedes recall and retention of this learning via decreased prediction errors and attention. We will also examine whether individual differences in pain sensitivity are associated with LI of conditioned fear acquisition, recall, and retention via greater engagement of these hypothesized mechanisms.

### Hypotheses

Hypothesis 1: (a) Preexposure to a stimulus will lead to diminished prediction errors in the outcome of the pre-exposed stimulus and diminished attention to the target stimulus and (b) to decreases in fear acquisition, recall, and retention.

Hypothesis 2: Changes in prediction errors and attention will mediate the effects of preexposure on fear acquisition, recall, and retention.

Hypothesis 3: Higher pain sensitivity will be correlated with greater engagement of the targeted mechanisms and therefore, greater LI of fear acquisition, recall, and retention.

## Methods and analyses

### Participants and setting

Participant enrollment will occur at two university sites—one in northwest Ohio and one in south Texas. Based on a power analysis, we aim to recruit 100 participants from the general community, ranging in age from 6 to 35 years old. Full eligibility requirements are presented in Table 1. Participants will complete two in-person study visits and receive a $50 gift card at each visit completed.

**Table 1 Tab1:** Participant eligibility criteria

Inclusion criteria	Exclusion criteria
Be between the ages of 6 and 35 years old	Currently have glasses or use contact lenses with a vision correction of ≥ ± 6
At least 2 of their maxillary anterior 6 teeth present	Are colorblind
All of their maxillary anterior 6 teeth are stable	Current injury (including fractures, open cuts, or sores) on their dominant hand
All of their maxillary anterior 6 teeth are free of cavities	Fixed dental or orthodontic appliance that would interfer with creating a mouthpiece
All of their maxillary anterior 6 teeth are free of hypersensitivity to pain or pressure	Diagnosis by a dental/oral health professional of Temporomandibular Disorder (TMD) along with a history of exacerbation of symptoms resulting from routine dental procedures
Able to read, write, and converse in English (English or Spanish at Texas site)	Currently on any anti-anxiety or anti-depressant medications
Willing and able to provide a signed and dated informed consent/assent form to participate	Currently have an inner ear infection
Willing and available to comply with all study procedures and available for the duration of the study	Living in the same household or an immediate family member of an enrolled participant
	Currently have a cardiovascular disorder or a pacemaker
	Currently have a seizure disorder or epilepsy
	History of frostbite or sensitivity to extreme cold
	Bleeding disorder or take blood thinners
	Vasospastic disorder such as Raynaud's syndrome or Raynaud's disease
	Gastrointestinal or vestibular disorders that may elevate susceptibility to nausea and dizziness such as Meniere's disease, hyperemesis gravidarum or severe migraines
	Negative outcome with VR simulation
	Medical or psychological condition that requires them to avoid mild stress
	Any medical condition that elevates risk of falls, dizziness, nausea, or causes a vasovagal reaction
	Any other general or oral health concerns

Special attempts to include Hispanic and African American participants will be made given the evidence that these populations are at greater risk for dental fear. The Ohio recruitment site will include participants from Toledo, Ohio and Detroit, Michigan. Together, these cities and the surrounding communities have a population of approximately 5 million, with approximately 22% of the population consisting of African American individuals [12]. The Texas site includes a population of 1.4 million, with 89% of the population consisting of Hispanic individuals [13].

### Study design and overview of procedures

Study variables include one measured subject variable (pain sensitivity) and two within-subjects manipulated variables [stimulus type: pre-exposed to-be conditioned stimulus (CS^+^_P_), non- pre-exposed to-be conditioned stimulus (CS_NP_^+^), and a never-conditioned stimulus (CS^−^)] and time [trial number].

After providing verbal consent, potential participants^1^ will complete a phone screen to assess eligibility. Interested participants meeting criteria will then participate in two study visits, approximately one week apart (min = 7 days,). Each visit will last approximately 90 min.

Visit 1 will begin with the completion of the consent and assent (if applicable) process, and confirmation of eligibility. Participants will then complete the measures and behavioural tasks described below as well as the experimental task. During the experimental task, the pre-exposure intervention will be administered, and fear conditioning procedures will be conducted. Immediately following, conditioned fear recall will be assessed; a minimum of 7 days later, fear retention will be assessed at Visit 2.

### Experimental task

#### Overview

The experimental task will be presented in virtual reality, via the HTC Vive Pro headset [14] with programming done in Vizard [15]. Use of a novel immersive environment in virtual reality allows for the control of pre-exposure (i.e., stimulus novelty) and for the assessment of approach/avoidance behavior. The task will be presented as a game in which the participant is marooned on an unfamiliar planet (see Fig. 2). The goal of the game is to collect enough fuel to return home. Participants will be told that this planet works differently from Earth, the experiences they have on the planet and with its inhabitants may not follow the same rules, and that some of the interactions on the planet may be somewhat uncomfortable. These instructions are meant to activate schemas related to pain sensitivity, paralleling experiences at a dental visit, and they also provide a rationale for the mouthpiece that the participant wears during the experimental task.

**Fig. 2 Fig2:**
[figure not shown]
Example scene from VR task

#### Stimuli

##### Aliens

Three novel aliens will serve as the CS_P_^+^, CS_NP_^+^, and CS^−^. The aliens were created for the project to ensure novelty and selected based on piloting with children, adolescents and adults which showed them to be perceived similarly and as relatively neutral; nevertheless, counterbalancing procedures will be used to rule out any stimulus-specific effects.

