### Analyses

SPSS software will be used to address the first and third hypotheses described below; Mplus software will be used to address the second hypothesis.

Hypothesis 1a: Preexposure to a stimulus will lead to diminished prediction errors in the outcome of the pre-exposed stimulus and diminished attention to the target stimulus.

The changes expected in the candidate mediators should first be observed during the pre-exposure phase. To test hypothesis 1a effects during this phase, two separate one-way repeated measures ANOVAs (with trials during the pre-exposure phase as the factor) will be run, one with attention during pre-exposure serving as the dependent variable and the second with prediction errors during pre-exposure serving as the dependent variable. To describe the change across trials, we will examine a plot of the mean responses across trials and test for the mean change from the first to the last trial in which the mediators are assessed. The Greenhouse–Geisser adjustment will be used to address possible violations of the sphericity assumption.

To examine the effects of preexposure on the candidate mediators during the conditioning phase, attention and prediction errors captured during conditioning trials will serve as dependent variables in two separate two-way (stimulus type X trial) repeated measures ANOVAs. If a significant stimulus x trial interaction is found in these analyses, stimulus type differences will be examined at each trial (using Bonferroni-adjusted alpha), and we will examine a plot of the mean response by stimulus type and trial.

In the recall and retention phases, scores on each of the candidate mediators will be averaged across trials and a one-way within-subjects ANOVA, with stimulus type as the factor, will be conducted separately for each outcome. Significant effects will be followed-up with paired samples *t*-tests to assess for specific differences between the stimulus types.

Hypothesis 1b: Pre-exposure to a stimulus will lead to decreases in fear acquisition, recall, and retention.

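### The aliens are counterbalanced, but no planned model contains alien or arrangement: a small precision loss for the mean contrasts, and a possible bias in the Hypothesis 2 mediation models

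*Protocol article*

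**What the plan says.** The Aliens subsection of the protocol article states that "Three novel aliens will serve as the" pre-exposed conditioned stimulus (CS+P), the non-pre-exposed conditioned stimulus (CS+NP) and the never-conditioned stimulus (CS-). The aliens were "selected based on piloting with children, adolescents and adults which showed them to be perceived similarly and as relatively neutral". Even so, "counterbalancing procedures will be used to rule out any stimulus-specific effects". The scheme is not described.

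The Study design section lists pain sensitivity, stimulus type and trial as the study variables. The Analyses section then names the terms of each model:

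- Conditioning phase: "two separate two-way (stimulus type X trial) repeated measures ANOVAs".
- Recall and retention: "a one-way within-subjects ANOVA, with stimulus type as the factor, will be conducted separately for each outcome".
- Hypothesis 1b: the same models, with the fear indicators as outcomes.
- Hypothesis 2: stimulus type and the two candidate mediators.
- Hypothesis 3: the same analyses with pain sensitivity as a moderator.

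Alien identity and counterbalancing arrangement appear in none of them.

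**The concern.** Counterbalancing makes the alien-to-role arrangement a factor of the design, and a factor built into the design normally belongs in the analysis. Leaving it out has two separate consequences.

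For the mean contrasts, chiefly CS+P minus CS+NP (the latent inhibition contrast), any difference between aliens enters each person's difference score and is counted as error.

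For mediation, the alien may affect both mediator and outcome. A more striking alien could attract longer dwell time and also provoke more fear. Balance across roles makes alien unrelated to stimulus type, but not to the mediator. The path from mediator to fear could then partly reflect which alien was shown. Identifying the mechanisms is the stated aim of the study, so this second consequence is the more useful one to address.

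**Working it through.** **Inputs.** From the document: three aliens, three roles, a target of 100 participants, and the model terms listed above. The inputs to the power analysis are not given, so the 100 cannot be reproduced; nothing below depends on doing so. Assumed, because the article gives no figures: alien means of -d, 0 and +d in SD units, with d from 0.1 to 0.4; a within-person correlation rho of 0.5 (0.7 as a variant); one arrangement per participant.

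**Step 1: bias in the mean contrast.** Over all six arrangements the alien part of CS+P minus CS+NP takes the values ±d, ±d and ±2d, with mean 0. Over a three-row Latin square it is -d, -d and +2d, again with mean 0. So equal filling removes the bias under either scheme. With 100 participants over six arrangements, 4 are left over (100 = 6 × 16 + 4). The worst four sum to 2d + d + d - d = 3d, so the remaining bias is at most 3d/100 = 0.03d. One fixed arrangement for everyone could give 2d.

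**Step 2: error variance in the mean contrast.** The mean square of the alien part is (1 + 1 + 4 + 4 + 1 + 1)d²/6 = 2d² for six arrangements, and (1 + 1 + 4)d²/3 = 2d² for the Latin square. The other variance of the difference is 2(1 - rho). The relative increase is d²/(1 - rho), and the equivalent sample size is 100/(1 + d²/(1 - rho)).

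| d | increase, rho = 0.5 | equivalent n of 100 |
|---|---|---|
| 0.1 | 2% | 98 |
| 0.2 | 8% | 93 |
| 0.3 | 18% | 85 |
| 0.4 | 32% | 76 |

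At rho = 0.7 and d = 0.3 the increase is 0.09/0.3 = 30%, so the equivalent n is 77.

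**Step 3: behaviour of the test.** The paired contrast was simulated (N = 96, all six arrangements equally filled, true effect 0.3 SD of the difference, two-sided 5% level, 4000 runs). Here s is the SD of the alien effects in units of the SD of the difference; at rho = 0.5, s = d × √(2/3), about 0.82d.

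- The mean estimate stays at 0.30 at every s.
- Power without an alien term is 0.83 at s = 0, 0.80 at s = 0.2, 0.74 at s = 0.35 and 0.63 at s = 0.5. With the term it is 0.83 to 0.84.
- With no true effect, rejection without the term is 0.05 at s = 0, 0.041 at s = 0.2 and 0.009 at s = 0.5. With the term it is about 0.05.

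The omission makes the test conservative. It does not create stimulus effects.

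**Step 4: mediation.** Assume one mediator, perfectly balanced arrangements, N = 96, rho = 0.5, alien effects of the same size and direction on mediator and outcome, and no true mediator-to-outcome effect. In a within-person regression the alien sum of squares per person is d² + 0 + d² = 2d², and the error sum of squares is 2(1 - rho). Without an alien term, the estimated mediator-to-outcome slope tends to d²/(d² + 1 - rho) instead of 0:

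| d | spurious slope | false indirect effects, no alien term |
|---|---|---|
| 0.1 | 0.01/0.51 = 0.02 | about 3% |
| 0.2 | 0.04/0.54 = 0.07 | about 13% |
| 0.3 | 0.09/0.59 = 0.15 | about 48% |
| 0.4 | 0.16/0.66 = 0.24 | about 87% |

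The last column is the simulated rejection rate of the z test when stimulus type shifts the mediator by 0.5 SD. With an alien term the rate is 3% to 4% throughout. Alien effects of opposite sign on mediator and outcome would push the slope the other way and could hide a true indirect effect. The planned Bayesian check would not reveal this if it fits the same terms.

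**The case against.** The strongest reply is that counterbalancing does what the article claims. Read naturally, the sentence means that alien identity cannot explain a mean difference between stimulus types, and Step 1 bears that out without any model term. This stands. A reader might infer from the missing term that a latent inhibition effect could really be an alien effect, or that 100 not dividing by six introduces bias. The document supports neither: the leftover bias is at most 0.03d and the test is conservative. A reader might also infer that alien role is confounded with pain sensitivity under Hypothesis 3. Nothing suggests that arrangement depends on pain sensitivity, so any imbalance would be chance.

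Second, the aliens are described as perceived similarly, so d = 0.3 or 0.4 (extreme aliens 0.6 or 0.8 SD apart) may be too large. This also stands in part and favours the low rows of both tables. The article does not report whether the piloting covered dwell time, distance or skin conductance.

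Third, a condensed article may leave such a term to the full protocol or analysis plan, and the scheme is not stated. It is fair to say that nothing is contradicted. But the article does name the terms of its models, so adding one is a concrete suggestion, and Steps 1 and 2 give the same mean and variance under three or six equally filled arrangements.

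Fourth, an arrangement main effect alone would gain nothing, because it is constant within a person and cancels from the difference. That is correct, and the fix below allows for it.

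**Conclusion.** This is a cheap improvement, not an error in the main contrasts. For the mean stimulus-type comparisons, counterbalancing removes alien bias provided the arrangements are about equally filled. The cost is precision: minor at d = 0.1 to 0.2 and noticeable only if the aliens differ more than the piloting suggests. For Hypothesis 2 the omission can bias the mediator-to-outcome path, and balance does not protect against that. In the assumed setting the effect is negligible at d = 0.1, visible at d = 0.2 and serious from d = 0.3. It requires that alien affects both mediator and outcome, which the document neither shows nor excludes. All sizes rest on the assumed d, rho and one-mediator model. It would go too far to say that stimulus-specific effects are left uncontrolled throughout the study.

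**What to change.** - **Repeated-measures ANOVAs (Hypotheses 1a and 1b, all stimulus-type comparisons):** enter counterbalancing arrangement as a between-subjects factor together with its interaction with stimulus type. Alternatively, use a mixed model with alien identity as a within-person term.
- **Mediation models (Hypothesis 2):** add alien identity as a covariate of both the mediators and the outcome.
- **Pain-sensitivity models (Hypothesis 3):** carry the same term through.
- **Description:** state the counterbalancing scheme in a sentence, so that the number of arrangements is known.

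The cost is 2 degrees of freedom for alien identity or, for arrangement, the number of arrangements minus one per contrast (5 if there are six, 2 if there are three), and slightly more complex models. The alien shown in each role is fixed by the design, so no new data or procedures are needed.

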**Fig. 3 Fig3:**
[figure not shown]
Dental startle equipment

### Procedure

Although the participant will experience the “game” seamlessly, the task is broken up into four phases: pre-exposure, conditioning, and recall phases, administered during Visit 1, and a retention phase, administered during Visit 2. Each phase can be further broken down into a series of trials, which we describe next.

The *pre-exposure phase* consists of 12 trials. Each trial begins with a minimum of six seconds in which the participant is free to roam the planet using the HTC Vive Pro controllers to collect fuel hidden in the environment. At the completion of this phase of the trial an algorithm is set to deliver the CS^+^_P_, accompanied by a fuel canister, at the first opportunity.^2^ The CS^+^_P_ and the fuel canister will appear at a fixed distance from the participant. The CS^+^_P_ remains for the last six seconds of the trial. During pre-exposure, the CS^+^_P_ is never accompanied by the UCS.

The *conditioning phase* is made up of 36 trials (12 CS_P_^+^ trials, 12 CS^+^_NP_, and 12 CS^−^ trials) presented in a pseudo-random order. These trials follow the same structure as those in the pre-exposure phase with the exception that 75% of CS^+^_P_ trials, and 75% of CS^+^_NP_ are accompanied by a dental startle (described below). More specifically, the dental startle will be delivered during the last 100 ms of the trial, with the startle and alien co-terminating. The CS^−^ is never presented with the dental startle.

In the fear *recall phase* 12 trials (4 CS^+^_P_ trials, 4 CS^+^_NP_, and 4 CS^−^ trials) are presented. Again, these trials follow the structure described in the pre-exposure and conditioning phases; however, none of the aliens are presented with the UCS.

Fear retention will be assessed in the *retention phase*—a repeat of the recall phase administered a minimum of 7 days later.

